### Outcome measures

#### Primary and secondary measures

Table 3 shows the primary and secondary outcome measures. The primary outcome measure is the presence and severity of psychological distress or disorder across four time points assessed by a mixture of psychometric mental health measures and diagnostic interviews based on criteria of the fifth edition of the *Diagnostic and Statistical Manual of Mental Disorders* for depression, anxiety and post-traumatic stress disorder. Secondary outcome measures will include motor vehicle crash injury history, employment, social life, resilience and self-efficacy, as well as indicators of physical health and lifestyle.

**Table 3 Tab3:** Primary and secondary outcome measures acrossbaseline, post-treatment and follow-up

Measure	Primary	Secondary	Baseline	3 months	6 and 12 months
Demographics					
Sex, age, weight, height		×	×		
Marital status		×	×		
Highest level of education		×	×		
Motor vehicle crash history					
Motor vehicle crash date		×	×		
Driver or passenger		×	×		
Perception of danger during motor vehicle crash		×	×		
Hospital admission: yes or no		×	×		
Days spent in hospital		×	×		
Involvement of lawyer		×		×	
Referral to psychologist or psychiatrist		×		×	
Satisfaction with claims process: 3-point Likert scale		×			×
Claim finalization: yes or no		×			×
Employment					
Pre-motor vehicle crash employment: part-time, full-time, pensioner		×	×		
Modified hours since motor vehicle crash: yes or no		×	×	×	×
Returned to work: yes or no		×	×	×	×
Expectation of return to work: 11-point Likert scale		×	×	×	×
Reason for non-return to work		×	×	×	×
Number of days after motor vehicle crash for return to work		×	×	×	×
Social life					
Returned to activities after motor vehicle crash: yes or no		×	×	×	×
Expectation of return to pre-motor vehicle crash activities: 11-point Likert scale		×	×	×	×
Pre-motor vehicle crash social activity quality		×	×	×	×
Satisfaction of pre-motor vehicle crash social supports: 11-point Likert scale		×	×	×	×
Satisfaction of pre-motor vehicle crash social engagements		×	×	×	×
Expectation of return to pre-motor vehicle crash activities: 11-point Likert scale		×	×	×	×
Pre-motor vehicle crash relationship quality: 5-point Likert scale		×	×	×	×
Lifestyle habits					
Alcohol: Alcohol Use Disorders Identification Test	×		×	×	×
Smoker: yes, no, amount per day		×	×	×	×
Health					
Health Status: SF-12		×	×	×	×
Psychology or psychiatric history: yes or no		×	×	×	×
Mood medication history: yes or no		×	×	×	×
Motor vehicle crash self-blame: 11-point Likert scale		×	×	×	×
Motor vehicle crash others-blame: 11-point Likert scale		×	×	×	×
Motor vehicle crash: perception of risk of own death: 11-point Likert scale		×	×	×	×
Coping capacity: The COPE		×	×	×	×
Pain: 11-point Likert scale		×	×	×	×
Pain catastrophizing: Pain Catastrophizing Scale		×	×	×	×
Impact of motor vehicle crash: Impact of Event Scale		×	×	×	×
Mood: Depression Anxiety Stress Scale 21	×		×	×	×
Resilience: Connor–Davidson Resilience Scale		×	×	×	×
Mood states: Profile of Mood States	×		×	×	×
*Diagnostic and Statistical Manual of Mental Disorders* Mini Plus Scores	×		×	×	×
Depression	×		×	×	×
Anxiety	×		×	×	×
Panic	×		×	×	×
Specific phobias	×		×	×	×
Post-traumatic stress disorder	×		×	×	×
Suicidal thoughts: yes or no	×		×	×	×

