### Sample size

Based on prior results of CBT and healthy lifestyle interventions [1, 4, 5], the two interventions are assumed to have at least a small to moderate mean effect size of 0.25 (Cohen’s *d*) when compared with the control group. Assuming an α probability of 0.05 and a power of 80 % for a three-group comparison analysis with four measures over time, a sample of 135 participants must be recruited to detect a true difference (see Fig. 1). It is therefore proposed to recruit at least 180 adult participants, randomly assigned to one of the three groups each with at least 60 participants per group. This is to accommodate for the loss to follow-up of approximately 25 % of participants, based on similar research [27].

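### The text describes one primary outcome but Table 3 marks nine or ten rows as primary, including alcohol use, and nothing fixes which result decides, so the 5 % error rate is not secured

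*Protocol article*

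**What the plan says.** Under Primary and secondary measures, the protocol article speaks of one primary outcome measure, psychological distress or disorder over four time points. It is "assessed by a mixture of psychometric mental health measures and diagnostic interviews", and the interviews are tied to depression, anxiety and post-traumatic stress disorder. The same paragraph lists the secondary outcomes, "as well as indicators of physical health and lifestyle" among them. The Abstract also places lifestyle factors with the secondary outcomes.

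Table 3 has a tick in its Primary column for these rows:

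- "Alcohol: Alcohol Use Disorders Identification Test", in the lifestyle habits block
- the Depression Anxiety Stress Scale 21 (DASS-21)
- the Profile of Mood States
- the Mini Plus line
- depression, anxiety, panic, specific phobias and post-traumatic stress disorder
- "Suicidal thoughts: yes or no"

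The Sample size section gives one error level, "Assuming an α probability of 0.05 and a power of 80" %, "for a three-group comparison analysis with four measures over time". It names no outcome variable. Hypothesis and data analysis states that both interventions are expected to prevent distress. It plans repeated-measures multivariate analyses of variance, but does not list the measures that enter them or say which test answers the primary question.

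**The concern.** The primary outcome is defined twice in the same section, and the two definitions differ. The plainest conflict is the alcohol test: primary in the table, yet filed under a heading that the text makes secondary. Panic, specific phobias and suicidal thoughts are ticked as primary but absent from the text's description.

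The text's own definition does not identify a variable either. A mixture of scales and interviews over four time points could be read as a score, a diagnosis, a set of scores or a composite, judged at any visit. As the document stands, a favourable result on any ticked row, for either intervention, could be reported as a positive primary finding, and the single 0.05 would not describe how often that happens by chance.

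**Working it through.** **The plan's own figures.** 135 / (1 − 0.25) = 180, so the allowance for loss to follow-up reproduces. The 135 cannot be confirmed from the stated inputs, because the within-person correlation is not given in the text and the power figure is not shown. It is matched by the between-groups test of a repeated-measures analysis of one outcome (3 groups, 4 measures) if 0.25 is read as Cohen's f and the correlation is taken as 0.8: noncentrality 135 × 0.25² × 4 / (1 + 3 × 0.8) = 9.93 on 2 and 132 degrees of freedom. The article labels the 0.25 as Cohen's d; that is a separate matter. What matters here is that no division of alpha is stated.

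**Counting the rows.** Table 3 has ten ticks in the Primary column. If the Mini Plus line is only a heading for the rows beneath it, nine remain. The check uses nine, the more lenient count.

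**Independent measures, one test each.** The chance of at least one false positive is 1 − (1 − 0.05)^k.

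- k = 9: 1 − 0.95⁹ = 0.370
- k = 10: 1 − 0.95¹⁰ = 0.401

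**Correlated measures.** The article gives no correlations between outcomes, so a range is assumed. For one comparison, each measure's null statistic was simulated as Z_j = √ρ·G + √(1−ρ)·E_j, with G and E_j standard normal, and rejected when |Z_j| > 1.96. For both comparisons, three arm vectors a, b and c (control) were drawn in the same way, with statistics (a − c)/√2 and (b − c)/√2, so that the control is shared. The omnibus column tests all three groups at once on each row (chi-square, 2 degrees of freedom).

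| Assumed correlation | Nine rows, one active-control comparison | Nine rows, one omnibus test each | Nine rows, both active-control comparisons |
|---|---|---|---|
| 0 | 37 % | 37 % | 58 % |
| 0.3 | 33 % | 33 % | 52 % |
| 0.5 | 27 % | 28 % | 44 % |
| 0.7 | 20 % | 21 % | 34 % |

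With ten rows the one-comparison column becomes 40, 35, 29 and 21 %. At a correlation of 0.9, nine rows and one comparison still give 12 %.

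**Visits.** The table above is for one visit. Table 3 schedules the ticked rows at 3, 6 and 12 months. However, Interventions offers controls a programme after their 6-month assessment, and Methods/design describes 12-month assessment only for controls who decline one. The full randomised control is therefore available at two post-baseline visits. Further visits add to the error only if they are tested separately.

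**Levels that would hold 5 %.** By Bonferroni: 0.05/9 = 0.0056 for nine tests and 0.05/18 = 0.0028 for nine measures with two comparisons each. A single designated primary test, or one committed global test, keeps 0.05.

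**The case against.** The strongest reply is that the calculation does not describe the stated plan. The article plans multivariate analyses, not nine separate tests, and one global test over the measures would hold 5 %. This stands as a limit on the arithmetic: the percentages describe what could happen under separate testing, not the error rate of a specified procedure. It does not remove the point, because the article speaks of analyses in the plural, lists no components and names no deciding test.

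It can also be said that multiplicity detail belongs in an analysis plan, and that a mixture implies several instruments. Both are fair. But an analysis plan cannot reconcile two conflicting definitions without changing one of them. The direct contradiction is the alcohol test; for panic, phobias and suicidal thoughts the text is silent rather than opposed.

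A reader might infer more than the documents support:

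- **That a false-positive primary result is likely.** In the table it exceeds one half only when both comparisons are tested on every row and the correlation is 0.3 or lower. That is hard to believe throughout a list with two mood scales and the depression and anxiety interviews.
- **That multivariate analysis is ruled out because the diagnoses are yes/no.** Among the ticked rows only suicidal thoughts is labelled so, and the Mini Plus line refers to scores. Binary diagnoses are plausible but not stated.
- **That the sample size was computed for one measure.** The section does not say this.
- **That three post-baseline visits each carry a full control comparison.** Only those up to 6 months do.

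**Conclusion.** The point holds as a contradiction and a poorly fixed primary outcome. Nine or ten rows are marked primary against one outcome in the text, the alcohol test conflicts with the text directly, and no measure, visit or test is named as decisive. The 5 % error rate is not secured.

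If the nine rows were tested separately at one visit, the chance of at least one false-positive primary result would be about 20 to 37 % for one active-control comparison and 34 to 58 % over both. That is substantial inflation, but not a result more likely than not in most of the range. The figures rest on assumed equal correlations of 0.7 down to 0, a two-sided 0.05 per test, and separate testing, which the article neither commits to nor excludes. The contradiction itself rests on no assumption. It should be settled before analysis, because until then the document does not say which result answers the trial's question.

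**What to change.** Before analysis:

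1. Name one primary variable and one visit with an intact control group, so no later than 6 months. The DASS-21 total is one example. A disorder-based variable or a single committed global test is another, and would suit a sponsor who wants post-traumatic stress disorder or presence of disorder to stay in the primary outcome, since the DASS-21 alone drops both. State the visit's starting point too: the Abstract counts follow-up from injury, Methods/design from study entry.
2. Test each active arm against control, with Holm over the two comparisons.
3. Move the alcohol test and the other ticked rows to secondary. If several primaries are kept, apply Holm over all retained measures and both comparisons (18 tests if all nine stay).
4. Make the text, Table 3 and the Sample size section refer to the same variable.

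The cost is wording in the protocol, Table 3 and the registration; no new data are needed. The headline then rests on fewer measures, and sharing alpha lowers power somewhat. A two-sided comparison with 80 % power at 0.05 would have Φ(1.96 + 0.84 − 2.24) = Φ(0.56) ≈ 71 % at 0.025, and Holm lies between the two. The stated 80 % refers to a three-group comparison, so power should be restated for the test actually chosen.

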#### Process measures

Treatment acceptability will be assessed by determining satisfaction with the intervention based on telephone calls to participants during treatment, and by asking four questions after treatment:Overall, how satisfied were you with the programme?How satisfied were you with the modules and module summaries?Would you feel confident in recommending this treatment to a friend?Was it worth your time doing the programme?

Participants will respond to the first two questions using a five-point Likert scale, which will range from ‘very satisfied’ to ‘very dissatisfied’ and the second two questions with a simple ‘yes’ or ‘no’ response. These questions have been used in previous research to examine the acceptability of internet-delivered CBT and other similar low-intensity treatments amongst consumers with a range of different conditions and across a range of different age groups [28–30]. Treatment feasibility will be broadly assessed based on the preliminary outcomes achieved combined with the ease with which clients could be supported through the programme by the insurance regulatory agencies. Generalizability of the treatment will be assessed with reference to the percentage of people who enter the study compared with the total number to whom participation is offered, and the follow-up rate achieved.

#### Safety measures and endpoint

This study is being conducted by a clinical psychologist highly experienced in the assessment and treatment of mental health disorders, as part of a doctoral study. The occurrence of adverse events, such as severe episodes of anxiety, panic, depression of risk of self-harm during the interventions, are considered safety endpoint measures of this trial. The regular contact by the clinical psychologist will identify whether the safety endpoint measure is required by any participant and appropriate action as per accepted mental health clinical guidelines will be instigated.

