## Methods/design

This study is designed as a three-arm randomized controlled trial with two active interventions and one active waiting-list control. The first is a brief email-delivered CBT treatment, consisting of five modules delivered fortnightly. The second is a brief email-delivered lifestyle treatment, also consisting of five modules and delivered fortnightly. Both groups will also receive weekly telephone contact to encourage their engagement with their programmes. The active waiting-list control group will receive reading material about the claims process, and will also receive fortnightly follow-up phone calls; however, these calls will only involve brief discussions of their progress in the compensation scheme in addition to confirming that they are receiving their reading material. There will be four measurement points: baseline (within 12 weeks of the motor vehicle crash), post-treatment (within 2 weeks of cessation of the interventions), and 6-month and 12 month follow-up sessions for the treatment groups (from the time of entry into the study) with the final two assessments also including participant satisfaction and acceptability questionnaires. If participants in the waiting-list control group do not want to receive either of the intervention programmes, they will also be assessed at 12 months.

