### Interventions

All participants will be randomly assigned to one of three groups: (i) CBT, (ii) lifestyle or (iii) waiting-list control. For the two treatment groups, participants are delivered fortnightly modules presented in Microsoft PowerPoint presentation with homework worksheets and templates for self-monitoring and practising learnt skills. Emails are brief with two or three paragraphs containing three or four concise sentences as well as a brief case study followed by a weekly summary. At the beginning of every other week, participants are telephoned for a maximum 10 min conversation aimed at (i) encouraging the learning and practising of skills from the previous week, (ii) ‘normalizing’ the challenges of learning new skills, (iii) emphasizing that symptom reduction requires gentle but consistent practice of the skills over time, and (iv) reminding participants about unread materials. The control group is also emailed fortnightly; however, this is restricted to reading information relating to the claims process, and phone calls are aimed at ensuring they are receiving and reading this information. The control group will be offered the programme of their choice, or the programme analyzed as more efficacious after their 6-month follow-up assessment. The contents of each module for each group (original version, March 2015) are presented in Table 2.

**Table 2 Tab2:** Contents of modules for cognitive behaviour therapy, lifestyle and waiting-list control groups

	Cognitive behaviour therapy	Lifestyle	Control
1	Overview	Overview	Reading: ‘A guide for people injured in a motor vehicle crash’
2	Mood and slow breathing skills, self-monitoring	Goal setting and life pacing	Reading: ‘Overview of the claims process’
3	The art of distraction, applying distraction	Self-monitoring and changing unhelpful behaviours	Reading: ‘Obligations of the insurer’
4	Stress and helpful thinking, evidenced-based thinking	Sleep hygiene and sleep self-monitoring	Reading: ‘Obligations of the claimant’
5	Problem solving and conclusions, self-mastery, changeable versus unchangeable problems	Improving well-being through diet and physical exercise, social participation, daily activity schedule	Reading: ‘Finalizing a claim’

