### Hypothesis and data analysis

The primary hypotheses assert that brief interventions (CBT and healthy lifestyle) will prevent the development of psychological distress by improving psychological coping skills and healthy behaviours. A further hypothesis is that the intervention groups will show improved resilience and quality of life compared with the control group; however, we are not hypothesizing a significant difference between the treatment groups themselves.

The effectiveness of the interventions will be determined by conducting multivariate analyses of variance with repeated measures for revealing differences within and between groups, as well as reporting effect size changes. Potential confounding factors, such as pre-injury health and education, will be adjusted for in the analysis. Correlation analyses and multiple regression will also be used to analyse predictors of psychological distress over time. The intervention satisfaction questionnaire will be analyzed to assess participant satisfaction of the overall treatment approach. Clinically significant improvements or recovery will be determined by identifying the proportion of participants who demonstrate a significant reduction in their symptoms.

An interim analysis will re-evaluate the assumptions made for the study’s sample size calculation, with re-estimation made if required, unless the trial needs to be stopped as a result of significant and consistent indications of elevated psychological distress associated with the interventions, according to the safety measures and endpoint.

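### Safety events are to be picked up through the psychologist's contact, yet control calls are confined to the claims process, so ascertainment probably differs by arm

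*Protocol article*

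**What the plan says.** All references are to the protocol article.

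- **Endpoint and window.** Safety measures and endpoint lists severe anxiety, panic, depression and self-harm risk, and says that such events "during the interventions, are considered safety endpoint measures of this trial".
- **Detection.** The same section states one route: "The regular contact by the clinical psychologist will identify whether the safety endpoint measure is required by any participant".
- **Control calls.** Methods/design says "these calls will only involve brief discussions of their progress in the compensation scheme", together with a check that the reading material is arriving. Interventions agrees: "phone calls are aimed at ensuring they are receiving and reading this information".
- **Treatment-arm calls.** Interventions gives four aims: practising skills, normalizing the difficulty of learning them, reminders about unread material, and "emphasizing that symptom reduction requires gentle but consistent practice of the skills over time".
- **Use of the endpoint.** Hypothesis and data analysis allows the trial to be stopped for "significant and consistent indications of elevated psychological distress associated with the interventions, according to the safety measures and endpoint".
- **Structured measures.** Table 3 lists DASS-21, the Mini Plus modules and suicidal thoughts at baseline, 3 months, and 6 and 12 months, without distinction by arm.

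**The concern.** A call confined to claims matters is a poor instrument for detecting severe distress, yet the safety section relies on contact with participants to do that for everyone. In the treatment arms symptoms are a natural topic of the call. In the control arm they lie outside its stated scope.

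Two things are at stake. First, controls are promised a detection route that the description of their calls does not support. Second, Background expects up to 50 % of survivors to develop elevated distress within 6 months of the crash. Against that natural course, distress in treated participants is hard to attribute to the programmes without looking at controls. If control events are under-counted, that look is tilted towards apparent harm. A false signal could arise, or a true one could be dismissed as an artefact of detection.

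**Working it through.** **1. The passages side by side**

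| | Treatment arms | Control arm |
|---|---|---|
| Who is covered by safety detection | any participant | any participant |
| Stated route | psychologist's regular contact | psychologist's regular contact |
| Stated call content | skills, normalizing, symptom reduction, unread material | claims progress, receipt and reading of material |
| Safety question listed | none | none |

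The promise is the same in every arm, but the means are not. Because no arm has a listed safety question, the difference is one of degree.

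Call frequency may add to it. For the treatment arms Methods/design says "Both groups will also receive weekly telephone contact to encourage their engagement with their programmes", while Interventions says "At the beginning of every other week, participants are telephoned for a maximum 10 min conversation". Controls are called fortnightly. Over 10 weeks that is about 10 calls against 5 on the first version, and about 5 against 5 on the second. The point rests on call content and does not need the first version.

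**2. Timing of the structured measures**

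The safety window is the intervention period. Methods/design places the post-treatment assessment within 2 weeks after the interventions end. DASS-21, Mini Plus and suicidal thoughts therefore cannot substitute for detection during the window, and the safety section does not name them as its source.

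**3. Illustration of the possible bias**

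The article gives no event rate, detection rate or safety threshold, so there is no figure to reproduce. The only document inputs are 60 per arm (Sample size), hence 2 × 60 = 120 treated and 60 controls. All the rest is assumed:

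- the true risk p is the same in every arm, so there is no real harm;
- the share of events detected is s_T in both programmes and s_C in controls;
- expected detected events are 120 × p × s_T and 60 × p × s_C;
- the apparent risk ratio is (p × s_T)/(p × s_C) = s_T/s_C, whatever p is.

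For p = 0.10, s_T = 0.9, s_C = 0.3: 120 × 0.10 × 0.9 = 10.8 events (9 %) against 60 × 0.10 × 0.3 = 1.8 (3 %), ratio 3.0.

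The table gives the chance of a falsely significant excess in the treated arms. It sums binomial probabilities over all outcomes where the treated proportion is higher and a pooled z-test exceeds 1.96. The article prescribes no such test; it serves only as a yardstick.

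| s_T | s_C | Ratio | p = 5 % | p = 10 % | p = 20 % |
|---|---|---|---|---|---|
| 0.9 | 0.9 | 1.0 | 1.2 % | 2.1 % | 2.3 % |
| 0.9 | 0.6 | 1.5 | 3.0 % | 8.4 % | 16.7 % |
| 0.9 | 0.3 | 3.0 | 7.3 % | 29.2 % | 64.3 % |

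With s_T = 0.8 and p = 10 %, the ratio runs from 0.8/0.2 = 4.0 down to 0.8/0.8 = 1.0. The false-excess chance is about 21 % at s_C = 0.3, 5 % at s_C = 0.6 and 2 % at s_C = 0.8.

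**The case against.** Much of the case on the other side stands.

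- **No stated comparison.** A reader might infer that the stopping provision compares arms. The text names no comparator, count, threshold or test, and a link to the interventions could be judged case by case. The between-arm reading is implied at most.
- **Missed control events are not a stated fact.** Controls are telephoned fortnightly, the safety section covers everyone, and a control may volunteer distress. Regular contact is not defined as the scheduled calls alone. Under-detection is likely, not certain.
- **Treatment calls list no safety question either.** It would be wrong to read the plan as structured detection in two arms and none in the third.
- **Who makes the calls.** A reader might infer that the psychologist who detects events also delivers the programmes. The article does not say so, and the point does not need it.
- **The distress measures may inform stopping.** The stopping sentence speaks of psychological distress, which these instruments measure. It neither names nor excludes them.
- **The numbers are assumed.** A marked false signal needs a large detection gap. The 50 % in Background is an upper estimate of elevated distress over 6 months, not of severe episodes in 10 weeks.
- **An article condenses.** Call scripts and adverse-event procedures may sit in the full protocol, so their absence here is no finding.

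The last objection does not dispose of the point. The article does not merely leave out the content of control calls; it restricts that content expressly, and the restriction sits badly with the detection route it states elsewhere.

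**Conclusion.** The tension between the safety section and the description of control calls is real and should be resolved. Followed as written, the plan probably gives poorer safety ascertainment in controls than in treated participants. The direction of any resulting bias is towards apparent harm of the programmes; its size cannot be derived from the article. Under the assumed rates shown, the apparent risk ratio without true harm ranges from 1.0 to 4.0. With treated detection at 0.9, the chance of a falsely significant excess ranges from about 1 % to 64 %. These figures assume equal true risk in all arms, the same detection rate in both programmes, and a pooled comparison that the article does not specify.

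The stronger statements, that the stopping provision compares arms or that control events will be missed, go beyond the text.

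**What to change.** Reconcile Methods/design, Interventions, Safety measures and endpoint, and Hypothesis and data analysis so that safety events are ascertained in the same way in all three arms. One way is to delete the word *only* from the description of control calls and to use the same brief safety enquiry on scheduled calls in every arm. The two statements of treatment-arm call frequency should be settled at the same time.

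Report the DASS-21, Mini Plus and suicidal-thoughts data by coded arm at post-treatment, as supporting between-arm safety evidence. They should not replace the endpoint for events during the interventions. The stopping provision should say whether and how arms are compared; this point proposes no threshold and no change to the clinical response.

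The cost is protocol wording and about a minute per call, with no new instrument. Controls receive slightly more attention, but the added enquiry is equal in all arms.
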